#### Secondary outcomes

The secondary outcome indicators will be evaluated using the ATEC, which includes four aspects: (1) speech/language/communication, (2) sociability, (3) sensory/cognitive awareness, and (4) health/physical/behavior [30]. With a total of 77 items, each item is rated using a 3-point scale (never, sometimes, and always; recorded as 0, 1, and 2 points, respectively) or a 4-point scale (none, mild, moderate, and severe; recorded as 0, 1, 2, and 3 points respectively). The main purpose of this study is to clarify the improvement in children with ASD after Tuina therapy from different perspectives. The evaluation time points for this outcome are consistent with those of the primary outcomes.

#### Safety assessment

Although pediatric Tuina is a nature-based approach to healing without side effects, some adverse events (AEs) may occur during the treatment process due to medical errors. Skin damage is the most common AE during Tuina. To prevent AE occurrence, strict monitoring will be conducted. In the case of AEs, the researchers will record the time and severity of the AE and promptly deal with it.

### Participant timeline

We have designed the schedule for the recruitment, intervention, evaluation, and follow-up of the participants, as shown in Fig. 2.

**Fig. 2 Fig2:**
[figure not shown]
Study schedule for recruitment, interventions, outcome measurements

### Sample size estimation

The sample size calculation for this study should use a superiority test with two independent sample means to test the scientific hypothesis that both Tuina and conventional treatment are effective for treating children with ASD, but the efficacy of the Tuina treatment may be superior. According to the primary outcome, a difference of more than 5 in the CARS from before to after the intervention is considered to indicate effectiveness [29]. In our initial clinical study [31], the mean value of the difference in CARS from before to after the intervention was 7.5 in the Tuina group (*n* = 22) and 4.27 in the control group (*n* = 22), with a combined standard deviation of 4.43. The test of superiority was a one-sided test, with the test level set at *α* = 0.025 and *β* = 0.2, power=0.8 The ratio of sample size between the two groups was set at a ratio of 1:1, and the shedding rate was 10%. The above data were entered into the interface of “Sample Size Calculation” of the Meisi Medical APP (Shanghai Meisi Medical Technology Co.). Based on the results, 108 cases in each group were deemed necessary. This research is funded by the Hunan Provincial Department of Science and Technology and other institutions that seek to benefit children with ASD. Therefore, we plan to include 200 cases in each group, for a total of 400 cases.

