### Statistical analyses

All data will be analyzed using SPSS (version 21.0; IBM Corp., Armonk, NY, USA); further, all analyses will be conducted using a two-sided test. Normally and non-normally distributed measurement data will be analyzed using the *t*-test and rank-sum test, respectively. The significance level will be set at 5% [32].

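### The 108 per group does not follow from the printed inputs, which give about 34–35 with 10% loss; the trial is oversized relative to them, not underpowered

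*Protocol article*

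**What the plan says.** The Sample size estimation section of the protocol article says that the calculation "should use a superiority test with two independent sample means". From the investigators' initial study of 22 children per arm it takes the planning values: "the mean value of the difference in CARS from before to after the intervention was 7.5 in the Tuina group" and "4.27 in the control group", with a combined SD of 4.43. It adds "The test of superiority was a one-sided test" at alpha 0.025, with 80% power, equal allocation and 10% loss. These values went into a sample size app, and the result is reported as "Based on the results, 108 cases in each group were deemed necessary". Enrolment is then set at 200 per group (400 in all), with reference to the funding.

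The same paragraph also says that "a difference of more than 5 in the CARS from before to after the intervention is considered to indicate effectiveness". The Primary outcomes section shows what this 5 is: a cut-point for grading the CARS reduction before to after the intervention (below 5 ineffective, 5 to 10 effective, above 10 significant). No between-group superiority margin is stated anywhere.

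Under Statistical analyses, "all analyses will be conducted using a two-sided test" at the 5% level, by t-test or rank-sum test. No margin appears there either.

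**The concern.** Every input that a two-sample comparison of means needs is printed, so the figure can be checked directly. An assumed difference of 3.23 points with an SD of 4.43 is a standardised effect of 0.73, and an effect that large does not need 108 children per group for 80% power. Either an input was used that the text does not disclose, or a number was entered in the wrong place.

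At stake is the stated basis for the size of the trial on its primary outcome. A reader who takes the paragraph at face value will believe that 108 per group gives 80% power for the assumed effect. If the 5-point response rule was used as a margin, the calculation also answers a question that the analysis section does not ask.

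**Working it through.** **Inputs** (all from Sample size estimation): difference 7.5 − 4.27 = 3.23; SD 4.43; one-sided alpha 0.025 (z = 1.960); power 0.80 (z = 0.842); 1:1; loss 10%.

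**Formula:** n per group = 2 × (1.960 + 0.842)² × SD² / D², where D is the expected difference minus any margin.

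**1. Attempt to reproduce 108 from the printed inputs (margin 0, D = 3.23).**
- n = 2 × 7.849 × 19.62 / 10.43 = 29.5, so 30 per group.
- By exact t-test, power is 0.793 at 30 and 0.806 at 31, so 31 per group.
- With 10% loss: 30 × 1.1 = 33 and 30 / 0.9 = 33.3, so 34; 31 / 0.9 = 34.4, so 35. The range is 33–35.

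The figure is not reproduced. Varying the settings does not close the gap:

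| Setting | n per group | with 10% loss |
|---|---|---|
| As printed | 30 | 33–34 |
| Two-sided alpha 0.025 | 36 | 40 |
| Power 0.90 | 40 | 44–45 |
| Power 0.95 | 49 | 54–55 |

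**2. The route that does give 108 from printed numbers.** Put 5 in as a superiority margin:
- D = 3.23 − 5 = −1.77, and D² = 3.133.
- n = 2 × 7.849 × 19.62 / 3.133 = 98.3.
- 98.3 × 1.1 = 108.2, the stated 108. (98.3 / 0.9 = 109.3.)

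D is negative here: the expected difference lies below the margin. Squaring removes the sign, so the formula returns a plausible sample size for a hypothesis that the assumed effect does not satisfy.

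**3. Power of the planned margin-free test for a true difference of 3.23.** Power = P(Z < 3.23 / SE − 1.96), with SE = 4.43 × √(2/n).
- n = 108: SE = 0.603; 3.23 / 0.603 = 5.36; power 99.97%.
- n = 97 (108 less 10%): power 99.9%.
- n = 180 (200 less 10%): power above 99.99%.

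**4. What 200 per group delivers.** With 180 evaluable per group, SE = 4.43 × √(2/180) = 0.467.
- 80% power: (1.960 + 0.842) × 0.467 = 1.31 points.
- 90% power: (1.960 + 1.282) × 0.467 = 1.51 points.

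**5. Scale.** 108 / 35 is about 3.1. The planned 400, against 68–70 in total (2 × 34 to 2 × 35), is nearly six times what the stated inputs need.

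**The case against.** The best defence is that the error does no harm to the planned comparison. The only analysis described has no margin, 108 per group is more than enough for it, the 200 actually planned was set by reference to funding, and the Trial status section says that recruitment has ended. All of that stands, and it limits the consequence to the justification for the size. It does not make the printed figure right.

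Several stronger readings are tempting and should not be adopted:

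- **That 5 was certainly used as a margin.** The article never says so, and the app's entries are not shown. Undisclosed inputs could also give about 108: a margin near 1.45, an SD near 8, or 108 as a two-group total at 95% power (49 × 1.1 = 54 per group). The match at 108.2 makes the 5-point route the likeliest explanation, but it is an inference.
- **That the trial is underpowered.** Against a margin of 5, power at 108 per group would be about 5 in 10 million if the true difference were 3.23. No test against such a margin is planned, so this figure shows only why the margin would be invalid.
- **That the loss adjustment is wrong.** The text gives a 10% rate and no formula. The factor 1.1 belongs to the inferred route.
- **That one-sided planning contradicts two-sided testing.** One-sided 0.025 and two-sided 5% require the same sample size.

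The article also gives no power or detectable difference for 400. The full protocol or analysis plan may hold these, so their absence is not part of the finding.

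**Conclusion.** The point holds as an arithmetic error in the figure that the article reports as the required sample size. The printed inputs need 30 per group (31 by t-test), or 33–35 with loss, not 108. This rests on the stated difference, SD, alpha and power with a zero margin, which is the only superiority test that the text supports. That the 5-point response rule was misapplied as a between-group margin is probable but unproven.

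The direction is oversizing. The stated 80% power is wrong because the true figure for the assumed effect is above 99.9%. The comparison on the primary outcome is not weakened, but the sample size justification as printed is invalid.

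**What to change.** Restate the paragraph as zero-margin superiority: difference 3.23, SD 4.43, one-sided 0.025 (equivalent to the planned two-sided 5%), 80% power, 31 evaluable per group, 34–35 with 10% loss. Remove 5 as a between-group input and leave it as the response rule under Primary outcomes. If a margin was in fact used, state and justify it; it must lie below the expected difference of 3.23.

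Then say what the planned 200 per group delivers: with about 180 evaluable, 80% power for about 1.3 CARS points and 90% for about 1.5.

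The cost is one reworded paragraph. Enrolment and the planned test stay as they are.

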### Recruitment

To secure an adequate sample, subjects in this study will be recruited mainly from rehabilitation institutions for special children in Changsha. The sentinel rehabilitation institutions have a certain stability and are not easily dislodged. Therefore, we will mainly start from the contact institutions. We will obtain information of the relevant institutions by referring to the official website of the Hunan Disabled Persons’ Federation (http://www.hndpf.org/news/tzgg/202012/t20201228_14086695.html). We will then explain the study details to the person in charge of each institution through telephone communication and, after obtaining consent, visit the institutions and sign a cooperation agreement. The person in charge of the institution will set up contact between us and the parents of the children and publish the recruitment notice through WeChat groups and recruitment posters, and eligible children will be enrolled through the application. After the third-party institution determines which children are eligible for inclusion, we will present the study design at the institution to help the guardians of the affected children understand the purpose and significance of the study. Following this, the guardians will be asked to sign an informed consent form before inclusion of their child in the study.

### Allocation

A computer-generated random number table will be used by statisticians otherwise not involved in the study. After completing the basic data assessment of all children with ASD, the children will be randomly assigned to the Tuina and control groups in a 1:1 ratio. The treatment sequences will be provided to each Tuina physician in an opaque envelope, and only the Tuina physician will be aware of the grouping. The third-party assessors as well as the data analysts will not be aware of the treatment allocations.

### Data collection and management

All parents of children with ASD participating in the project will sign the informed consent form and complete the case report form. Finally, a data file will be established and will be kept and collected by a dedicated person from the Data Committee of the First Affiliated Hospital of the Hunan University of Chinese Medicine. It is important to emphasize that data custodians must maintain their independence and access and audit the data on a regular or irregular basis, thus ensuring that no one can tamper with the data. Inspectors will regularly check the informed consent form, research protocol, and evaluation scale to ensure the quality of the clinical research. Regarding the authenticity of the study, all involved researchers will be blinded to the data. Based on the data disclosure requirements of the *CHICTR*, the data of this study will be uploaded to the Baidu Cloud Disk or the website of the School of Acupuncture-Moxibustion and Tuina of Hunan University of Chinese Medicine (zjtn.hnucm.edu.cn) within 6 months after the study completion and will be made publicly available. The premise is that the main research results will be published. All nonmembers should sign an agreement form before accessing the research results.

### Statistical analyses

All data will be analyzed using SPSS (version 21.0; IBM Corp., Armonk, NY, USA); further, all analyses will be conducted using a two-sided test. Normally and non-normally distributed measurement data will be analyzed using the *t*-test and rank-sum test, respectively. The significance level will be set at 5% [32].

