**Methods:**

Eligible children will be randomly assigned to either the pediatric Tuina plus conventional treatment group or to the conventional treatment alone group based on a random table at a ratio of 1:1. The effectiveness of the Tuina intervention for ASD will be evaluated by a third-party organization. The pre- and post-intervention scores on the Childhood Autism Rating Scale comprised the primary outcome, whereas pre- and post-intervention scores on the Autism Treatment Evaluation Checklist were the secondary outcomes to assess improvement in symptoms. Baseline values of the participants will be determined at the time of registration. Outcomes will be evaluated after the 30th treatment session. The follow-up period will last for 6 months after treatment.

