### Participants

This study will recruit 400 children with ASD from autism organizations certified by the Hunan Disabled Persons' Federation, including Xingxueyuan Education Development Center (Tianxin District, Changsha City), Aimeng Rehabilitation Center for Special Children (Yuhua District), and Vitality Autism Rehabilitation Center (Yuelu District), among others.

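### The primary comparison is an unadjusted t-test or rank-sum test chosen by observed normality; one pre-specified ANCOVA on baseline CARS would fix the hypothesis and narrow the interval

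*Protocol article*

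**What the plan says.** The Statistical analyses section of the protocol article names the software, says "all analyses will be conducted using a two-sided test" at a 5% level, and gives one rule for continuous data: "Normally and non-normally distributed measurement data will be analyzed using the *t*-test and rank-sum test, respectively". It names no covariate and does not say whether the test is applied to end-of-treatment scores or to changes.

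Other sections narrow the reading:

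- Primary outcomes grades efficacy by the before-after difference in CARS.
- Sample size estimation uses a superiority test of two independent means, with mean CARS changes of 7.5 and 4.27 and a combined SD of 4.43. It states that "The test of superiority was a one-sided test", "with the test level set at *α* = 0.025 and *β* = 0.2, power=0.8".
- Baseline is available for every child. The abstract says "Baseline values of the participants will be determined at the time of registration", and a CARS score of at least 30 is an inclusion criterion.
- Participants says "This study will recruit 400 children with ASD from autism organizations certified by" the Hunan Disabled Persons' Federation, and names three centres among others. Allocation describes individual 1:1 randomisation and mentions no stratification.

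**The concern.** Two features of the stated rule matter.

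**The data choose the hypothesis.** A t-test compares means and yields the mean difference for which the trial is sized. A rank-sum test asks whether values in one arm tend to be larger than in the other, and does not estimate that mean difference. Unless the two distributions differ only by a shift, the answers need not agree. Which one becomes the primary result would depend on the shape of the observed data.

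**Baseline is used inefficiently.** If changes are tested, baseline is subtracted with a fixed slope of 1. ANCOVA estimates that slope, so it removes more of the outcome variance that baseline explains and corrects for chance imbalance between arms in baseline CARS.

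At stake are the width of the interval and the meaning of the reported effect.

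**Working it through.** **Inputs from the protocol article (Sample size estimation).** Difference in mean change 7.5 − 4.27 = 3.23; SD of change 4.43; one-sided α 0.025 (the same critical value, 1.96, as two-sided 5%); power 0.80; dropout 10%; 200 enrolled per arm, hence 200 × 0.9 = 180 analysed per arm.

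**Input not in the documents.** The correlation r between baseline and end-of-treatment CARS; assumed range 0.3 to 0.9.

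**Step 1. The plan's own figure.** n per arm = 2 × (1.96 + 0.842)² × 4.43² / 3.23² = 29.5, so 30, and 30/0.9 gives 34 with dropout. The protocol states 108. That figure does not follow from the stated inputs. It is a separate matter, and nothing below depends on it, because the planned enrolment is 200 per arm.

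**Step 2. Variances.** With equal pre and post variance s²:

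- change score: 2s²(1 − r)
- ANCOVA: s²(1 − r²)
- ratio: (1 − r²) / [2(1 − r)] = (1 + r)/2, a reduction of (1 − r)/2.

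**Step 3. Numbers at 180 per arm.** The standard error for the change-score t-test is 4.43 × √(2/180) = 0.467. For ANCOVA it is multiplied by √[(1 + r)/2]. The detectable difference at 80% power is (1.96 + 0.842) × SE.

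| Analysis | Variance ratio | SE | 95% half-width (1.96 × SE) | Detectable difference |
|---|---|---|---|---|
| t-test on change | 1 | 0.467 | 0.92 | 1.308 |
| ANCOVA, r = 0.3 | 0.65 | 0.376 | 0.74 | 1.055 |
| ANCOVA, r = 0.5 | 0.75 | 0.404 | 0.79 | 1.133 |
| ANCOVA, r = 0.7 | 0.85 | 0.431 | 0.84 | 1.206 |
| ANCOVA, r = 0.9 | 0.95 | 0.455 | 0.89 | 1.275 |

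**Step 4. Power at the planned effect.** Even with the change-score t-test, 3.23/0.467 = 6.9 standard errors, so power exceeds 99.9% with or without adjustment.

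**Step 5. The switch, by simulation.** 3,000 trials per scenario, 180 per arm, r = 0.7. The rank-sum test was used if a Shapiro-Wilk test rejected normality of the changes at 5% in either arm. This screen is an assumption, since the article names none. Skew was placed in the post-treatment errors (gamma, shape 10 for mild and 4 for stronger).

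| Errors | Sent to rank-sum (true difference 1.3) | Type I error, chosen test | Power at 1.3: t-test | Chosen test | ANCOVA |
|---|---|---|---|---|---|
| Normal | 9% | 4.9% | 79% | 79% | 86% |
| Mild skew | 87% | 4.1% | 79% | 80% | 85% |
| Stronger skew | 99.7% | 4.8% | 79% | 82% | 85% |

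At this sample size a formal screen picks up mild skew in most trials, so the rank test would often become the primary test. The t-test held its level in all three scenarios (4.3% to 4.8%), so the switch is not needed to protect validity.

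**The case against.** The strongest reply is that a t-test on change and an ANCOVA are both valid, that a condensed article may leave covariates to an analysis plan, and that power is ample. Much of this stands. The absence of a covariate list or of a normality criterion would not be a finding on its own. What can be reviewed is the rule that the article does state, and that rule makes the primary comparison depend on the observed distribution.

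Four stronger readings are tempting and are not supported:

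- **That baseline is ignored.** Primary outcomes and Sample size estimation both work with the before-after difference, so the natural reading is a test on changes, with baseline subtracted. Only a test on post scores alone would discard it. Under that less supported reading the ANCOVA variance ratio would be 1 − r², or 0.91 to 0.19 for r from 0.3 to 0.9. Those figures should not be used as the size of this point.
- **That institution is already a recorded variable.** Recruitment through institutions, and a drop-out criterion for changing institution, make it very likely to be known. No section lists it as a data item, and the gain from adjusting for it cannot be derived from the documents.
- **That the trial loses needed power.** A variance saving can be expressed as children, but at 3.23 and 4.43 power is above 99.9% either way, and the increase to 400 is explained by funding and benefit to children, not by a precision target.
- **That the switch inflates type I error.** The simulation gave 4.1% to 4.9%. Chance baseline imbalance is likewise not bias; the interval already covers it, only less tightly than it could.

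**Conclusion.** The point holds as an inexpensive improvement to a stated method, not as an error of validity. The primary hypothesis is not fully fixed, because distributional shape selects between means and ranks in a trial sized on means. Baseline CARS is not used as a covariate.

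Against a change-score t-test, ANCOVA cuts the variance by 35% (r = 0.3) to 5% (r = 0.9), taking the standard error from 0.467 to between 0.376 and 0.455 CARS points. This rests on an assumed r, on 180 analysed per arm and on equal pre and post variances. The last may not hold exactly: entry at CARS 30 or above restricts the baseline range but not the later one. If the post variance is larger, the slope on baseline moves towards 1 and the gain shrinks, vanishing when the slope equals 1. Apart from the single degree of freedom spent on the slope, ANCOVA is still no less precise than the change-score test. Power would matter only if the true difference were far below the 3.23 seen in a pilot of 22 per arm.

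**What to change.** Replace the distribution-based rule for the primary outcome with one pre-specified model, for example:

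*Primary analysis: linear model (ANCOVA) of CARS after session 30 on treatment arm and baseline CARS, reporting the adjusted mean difference with its 95% confidence interval, two-sided 5% level. The same model, with the matching baseline, is used for ATEC and for the 6-month ratings. The rank-sum test is a sensitivity analysis only and does not replace the primary result.*

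Institution may be added as a factor if it is recorded for every child; if so, any rule for combining small institutions should be written down before outcomes are seen.

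The cost is a few lines of wording. The core model needs no new data and runs in the named software. The Protocol amendments section gives the route: ethics committee approval, then an update of the registry entry. Trial status describes the trial as entering the intervention phase, so at that stage the change could still be fixed before outcomes were analysed.

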#### Elimination criteria

1. Children who do not complete 30 intervention sessions following the research protocol

2. Children who received other interventions that may affect the study results

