#### Primary outcomes

The main efficacy score will be based on the CARS, which covers interpersonal relationships, imitation, and other 15 aspects, with a total score of 60 points. Each aspect will be scored using a four-point scale: age-appropriate (score 0), mildly abnormal (score 1), moderately abnormal (score 2), and severely abnormal (score 3). Participants with a score < 30, 30–35, and ≥ 36 are considered as non-autistic, moderately autistic, and severely autistic, respectively. Outcomes will be evaluated after the 30th treatment session. Follow-up efficacy assessment will be performed at 6 months post-treatment. The difference in CARS before and after the intervention will be considered significant, effective, and ineffective if the reduction is greater than 10, 5–10 (inclusive), or less than 5 points, respectively [29]..

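### The named two-sample tests cannot use the session-30 score of a child with no 6-month score, so the 6-month comparison can be biased if later loss is outcome-related and differs between arms

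*Protocol article*

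**What the plan says.** The protocol article schedules two post-baseline efficacy assessments. Under Primary outcomes, for CARS: "Outcomes will be evaluated after the 30th treatment session", and then "Follow-up efficacy assessment will be performed at 6 months post-treatment". Under Secondary outcomes, for the Autism Treatment Evaluation Checklist (ATEC): "The evaluation time points for this outcome are consistent with those of the primary outcomes".

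Statistical analyses gives the tests: "Normally and non-normally distributed measurement data will be analyzed using the" t-test and the rank-sum test, in that order. It adds that "all analyses will be conducted using a two-sided test" and "The significance level will be set at 5" per cent. It names no model linking baseline, session-30 and 6-month scores, no analysis set and no method for missing scores.

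On loss, Sample size estimation says "the shedding rate was 10" per cent, without dividing it by arm or by time. The Elimination criteria list "Children who do not complete 30 intervention sessions following the research protocol". The Drop-out criteria include guardians who end treatment because they see no benefit, and children who leave or change their rehabilitation institution.

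**The concern.** The 6-month visit is the only stated efficacy assessment after the end of treatment, so any claim that an effect lasts rests on it. A two-sample test at that visit compares the children who have a 6-month score. A child scored after session 30 and lost afterwards contributes nothing, although the trial holds a measurement that would help to predict the missing one.

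The design makes outcome-related loss plausible. Study design rules out blinding, the child is held by parents or relatives during Tuina, and the Drop-out criteria themselves foresee departures over perceived lack of effect. If children who improved less leave one arm more readily, the remaining groups are selected differently and their 6-month means are no longer a fair comparison. This matters most where the true 6-month difference is near zero, because a small bias then raises the false-positive rate.

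**Working it through.** **The plan's own figure.** The only computed figure is 108 per group. It reproduces if the 5-point threshold is entered as a superiority margin: |3.23 − 5| = 1.77; n = 2 × [4.43 × (1.960 + 0.842) / 1.77]² = 98.3; 98.3 × 1.1 = 108.2. This point does not depend on it, and the fix changes no sample size.

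**Inputs from the protocol (Sample size estimation).** 200 per arm; mean CARS reductions 7.5 (Tuina) and 4.27 (control), difference 3.23; SD 4.43; 10% loss. The 5-point effectiveness threshold also stands under Primary outcomes.

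**Assumptions, not in the protocol.** Correlation ρ between session-30 and 6-month change of 0.5 to 0.8; the same SD at both visits; no true 6-month difference; all loss falls after session 30; controls lose 10% at random; Tuina loses a share p of children with under 5 points of reduction and 5% of the rest.

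**Formula.** With c = (5 − 7.5)/4.43 = −0.564, Φ(c) = 0.286 and φ(c) = 0.340:

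- Tuina loss L = p × 0.286 + 0.05 × 0.714
- Bias of the test on observed children = ρ × 4.43 × (p − 0.05) × 0.340 / (1 − L)
- SE = 4.43 × √[1/(200(1 − L)) + 1/180]
- Error rate = Φ(−1.96 + bias/SE) + Φ(−1.96 − bias/SE)

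| p | Tuina loss | Bias, ρ = 0.5 / 0.7 / 0.8 | SE | Two-sided error rate |
|---|---|---|---|---|
| 25% | 10.7% | 0.17 / 0.24 / 0.27 | 0.468 | 6.5% / 8.0% / 8.9% |
| 40% | 15.0% | 0.31 / 0.43 / 0.50 | 0.474 | 10.0% / 15.1% / 18.2% |

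Repeated simulations of these scenarios agree: bias 0.15 to 0.28 points with error rate 6.3 to 9.9% in the first row, and 0.30 to 0.52 points with 9.9 to 21% in the second. A likelihood estimate that uses the session-30 score stays within 0.03 points, with error rate 4.2 to 5.8%.

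**Same loss rule in both arms.** For controls c = (5 − 4.27)/4.43 = 0.165 and φ(c) = 0.394. With p = 25% in both arms, control loss is 16.3% and the bias is ρ × 4.43 × (0.0762 − 0.0941) = −0.04 to −0.06, with error rate 5.1 to 5.2%. With p = 40% in both arms it is −0.10 to −0.15.

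**A differently built check.** Here the chance of loss follows a logistic curve in the session-30 score (slope 1 per SD, also an assumption), the true difference is 3.23 and ρ = 0.6:

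- Same rate and same dependence in both arms (10% or 20%): about 0.
- 5% loss in control and 15% in Tuina: +0.23. Rates exchanged: −0.23.
- 10% per arm, dependence in Tuina only: +0.23 (0.17 at ρ = 0.4, 0.34 at ρ = 0.8). In control only: −0.23.
- Using the session-30 score: about 0 throughout (at most 0.02).

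**Loss before the session-30 score.** With the 25%/5% rule kept but the loss moved before that score, an estimate using post-treatment scores only is biased by 0.16, 0.24 and 0.27 points at ρ = 0.5, 0.7 and 0.8, the same as the two-sample test. With half the loss early, 0.08 to 0.13 points remain.

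**The case against.** The strongest objection is that the section is a few lines of a condensed article, and that missing-data handling and repeated-measures modelling are commonly left to an analysis plan, which is not shown. That stands as far as silence goes: the absence of a missing-data method is no error. The point concerns something else, namely the tests that the article does name for all measurement data, which cannot use the earlier score.

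Four stronger readings are tempting and are not supported:

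- That the protocol limits the 6-month test to children still present. It does not say so; this follows from the tests only if nothing is imputed.
- That the session-30 score predicts loss, or that loss differs by arm. Neither is stated.
- That the follow-up result will be biased in favour of Tuina. The sign depends on which arm loses poor responders more selectively, and the bias nearly vanishes when both arms behave alike.
- That nearly all children will have a session-30 score, so that a joint model repairs the problem. The 10% is not dated, and it inflates a sample size built on the change from before to after the intervention. The Elimination and Drop-out criteria place much of the named loss during treatment, and the model does not correct for those children.

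It is also fair that the bias is small beside 3.23 points, that the 15% scenario exceeds the plan's 10%, and that the comparison after session 30 is untouched.

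**Conclusion.** The point holds in conditional form. The named tests discard available information at 6 months unless missing scores are imputed. Bias follows only if loss after session 30 depends on the session-30 score and differs between arms in rate or in that dependence. Its size is then about 0.15 to 0.3 CARS points at about 10% loss and 0.3 to 0.5 at 15% in one arm, in either direction. If both arms lose children alike it is about 0. The correlation, the loss rule and its timing are all assumptions, and the CARS figures do not carry over to ATEC in points. Against an assumed difference of 3.23 this would rarely change a clear result; it could matter if the 6-month difference is near zero. This is a cheap improvement to a stated method, not a demonstrated bias.

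**What to change.** In Statistical analyses, replace the separate tests of CARS and ATEC with one mixed model for repeated measures for each scale:

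- Outcomes: the session-30 and 6-month scores.
- Terms: arm by visit and baseline score by visit, with unstructured covariance.
- Children: all those randomised who have any post-baseline score.
- Report: the arm difference at each visit with its 95% CI.
- Sensitivity analysis: keep the rank-sum test for non-normal data.

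The named software, SPSS 21, can fit this with its MIXED procedure.

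The cost is a change of wording and slightly more analysis work, with no new visits, data or sample size. The model relies on loss being explained by observed scores, which is a weaker assumption than a test on observed children makes. The text should say that the model does not correct for children lost before the session-30 score, and should report loss by arm separately before and after that visit so that readers can judge how much the model can address.
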